### Main outcome assessments (weeks 3–5)

While lead researchers will need to know participant allocation in order to advise bed time changes, the study administrator, researchers collecting outcome data and those conducting statistical analyses will be blinded to participant allocation. Data collection will occur at baseline (week 1) and during the two experimental weeks (weeks 3 and 5) to test the two sleep conditions (restriction and extension). Some measurements occur daily during intervention weeks (actigraphy), on 2 days (diet recalls, cameras) or only at the end of each experimental week (hunger experiment, food cravings, questionnaires).

#### Clinic visit: eating in the absence of hunger (EAH) feeding experiment (primary aim)

Our clinic-based feeding experiment in the late afternoon on the last day of each experimental week (weeks 3 and 5), will carefully measure eating in the absence of hunger objectively, by assessing first how participants report their preferences for certain foods via questionnaire, and then how participants consume treat foods under each sleep condition on a ‘full stomach’ [74]. Upon arrival at the clinic, caregivers and participants will complete a 24-h diet recall. The children will complete the Food Cravings Questionnaire and be weighed. They will then begin their pre-load meal which contains the pre-weighed and measured items listed in Table 3 and shown in Fig. 2**.** The pre-load meal will be offered as a buffet dinner, at which time they will eat ad-libitum until they are fully satisfied. When children appear to be replete, ongoing intake will be gently encouraged to assure children eat until they feel satisfied or ‘full’. The feeling of repletion will be assessed by a validated hunger and satiety visual 1–5 point rating scale called “Teddy the Bear” that is designed for primary school children [75]. Only those children who indicate fullness of 4 or 5 will be included in analyses to ensure children were full before the free access phase [76]. Once they are finished eating, the time will be noted and the child participant moved into a separate room for questionnaire completion. Based on other research, we piloted this protocol with a 15 min gap between the child finishing the pre-load meal, and beginning to eat in the free access phase [74], and we will continue this practice in the main study. Caregivers will complete their own questionnaires while the children complete the free access phase of the experiment, which contains the pre-weighed and measured items listed in Table 4 and Fig. 3, where participants will be given the opportunity to eat highly palatable snacks (e.g. lollies, chips, chocolate) for 15 min without adult supervision.

**Table 3 Tab3:** Foods offered during the pre-load phase of the Eating in the Absence of Hunger (EAH) experiment

Food item	Quantity (g)	Energy content (kJ) [1]
Pizza	300	3036
Cocktail sausages	240	2124
Tomato sauce	60	243
Barbeque sauce	60	415
White bread	122	1214
Margarine	30	726
Garlic aioli	90	999
Sliced ham	50	206
Processed cheese	42	542
Jam	45	453
Honey	45	545
Peanut butter	33	856
Fruit yoghurt (low fat, sweetened)	300	986
Dairy food yoghurt (low fat, sweetened)	300	1020
Banana	200	764
Apple (Eve, red)	200	434
Mandarins	170	323
Total		14,883 [2]

^1^ All values obtained from manufacturer’s Nutrition Information Panels (NIPS) except for fruit, for which values are from Kaiculator software

^2^ Total is > 100% estimated energy requirement (EER) for boys and girls aged 8-12 years [65]

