### Aims and objectives

The primary aim of the DREAM study is to determine whether mild sleep deprivation increases energy intake in the absence of hunger (measured objectively). Secondary aims will determine whether mild sleep deprivation: 1) influences the amount and types of foods eaten, 2) alters the context of eating (e.g. where, when, who with, what else is happening), 3) changes other indices of eating behaviour (e.g. emotional over-eating), 4) changes children’s preference for different food types, 5) changes how caregivers care for their child with regards to snacking and meals, and 6) influences time spent in sedentary or physical activity.

We hypothesize that, when compared to being well-rested, children whose sleep is restricted by one to 2 hrs per night will be less able to regulate their appetite, and will therefore eat more food, particularly at night, will eat for reasons other than hunger more often, will rate treat foods as more appealing, and will engage in more sedentary behaviour.

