### Baseline and randomisation

Eligible participants will be seen at a 45–60 min baseline appointment in their home (week 1, Table 1). Primary caregivers will provide written consent for minors at this time, as well as complete online questionnaires assessing demographics (child date of birth, date of survey, household address to calculate household deprivation, ethnicity, family structure), child food preferences and allergies (to plan for the feeding experiment in weeks 3 and 5), and the Children’s Sleep Hygiene Survey [63]. Consent will also be gained from each child participant. Height (Wedderburn Portable Height Rod, WS-HRP) and weight (Tanita electronic scales HD351) will be measured following standard procedures, and an actigraph (the ActiGraph wGT3X-BT) will be provided to be worn on the child’s right hip 24-h a day for 1 week to measure usual sleep, physical activity and sedentary behaviour, initialized with 15 s epochs.

Families will be provided with a Participant Instruction Booklet containing all study instructions. After the baseline appointment is complete, participants will be randomised to start with either sleep restriction or sleep extension during intervention weeks 3 and 5. Randomisation will be stratified by age (grouped by 8–10 and 11–12 years) and gender. Randomisation to order will be generated using random block lengths (Stata 15.1, StataCorp, Texas) and uploaded into the REDCap randomisation module [67].

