#### Questionnaires (end of each experimental week)

##### Changes in eating behaviour (secondary aim 3)

Primary caregivers will complete the 35-item Child Eating Behaviour Questionnaire (CEBQ) [64], which provides eight subscales including satiety responsiveness (how well they eat to appetite), food responsiveness (eating for reasons other than hunger), emotional over-eating (eating because of emotions), and fussiness. Questions will be adapted to reflect the past week.

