#### Feasibility and pilot work

A full DREAM pilot was undertaken in 11 children aged 8–12 years to determine acceptability and feasibility (University of Otago Human Ethics Committee reference #18/044). All but one child completed all measurements; the child with incomplete data was sick for several days during week 5. Analyses of completed actigraphy and sleep diaries demonstrated that children were 100% adherent to the protocols and mean time in bed was 1.5 h different between sleep restriction and extension conditions. Importantly, sleep was reduced by almost one hour per night during the restriction week, proving it is feasible to reduce sleep in this age group. The adherence findings in the DREAM pilot study are in line with others who also report high compliance (95%) with a similar protocol in children of this age [56]. In terms of our primary outcome, only two children had to be excluded from analyses as they did not indicate scores of 4 or 5 (indicating they were full) on the Teddy Bear scale at the end of the preload phase of the EAH feeding experiment. One child was unable (due to school regulations) to wear their camera for all hours during the prescribed days; this resulted in an overall 91% adherence to camera protocols.

Feedback from participants was overwhelmingly positive. Children loved being involved and “*felt very grown up recording their bed times”.* Several commented how they *“felt much better during the sleep extension week”* with caregivers commenting they noticed differences in their child’s behaviour that were enlightening as many had not really considered how sleep might influence behaviour or food intake. Overall caregivers felt the study burden was manageable, even though the sleep restriction week was difficult for some families.

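### The primary analysis keeps only children who rate themselves full, a response measured after the randomised sleep week, and no all-children analysis is planned beside it

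*Protocol article*

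**What the plan says.** In the section on the clinic visit and feeding experiment (primary aim), the protocol article states: "Only those children who indicate fullness of 4 or 5 will be included in analyses". The stated purpose is that the snack phase should start from satiety. The rating is a five-point pictorial scale, completed after an ad-libitum pre-load meal on the last day of weeks 3 and 5. It therefore follows seven nights of the assigned condition. *Baseline and randomisation* puts allocation earlier: "After the baseline appointment is complete, participants will be randomised to start with either sleep restriction or sleep extension".

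*Aims and objectives* gives the expected effect of treatment: "children whose sleep is restricted by one to 2 hrs per night will be less able to regulate their appetite, and will therefore eat more". Satiety responsiveness, a subscale of the caregiver eating-behaviour questionnaire, is also measured as an outcome at the end of each experimental week.

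*Feasibility and pilot work* shows the rule in use among 11 children: "only two children had to be excluded from analyses as they did not indicate scores of 4 or 5". It does not say in which sleep condition those ratings occurred.

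*Power calculations and statistical analyses* specifies a mixed model with participant as a random effect. It does not mention the fullness rule and gives no analysis that keeps the excluded children. Nothing in the article says whether a non-full rating at one visit removes that visit or the whole child.

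**The concern.** In a crossover, randomising the order makes the two conditions comparable as long as the children or visits analysed are not chosen by something the condition may have changed. Here inclusion in the primary analysis depends on a response recorded after treatment, in the same domain as the outcome. The child gives the rating and knows which bedtime was assigned; the blinding described covers staff and analysts.

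Suppose restriction makes some children harder to satiate, and those children also snack more in the free-access phase. The rule would then remove more high-intake visits under restriction than under extension, and the estimated difference would shrink.

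The crossover does not cure this. Dropping the child restricts the contrast to children who are full under both conditions. Dropping only the visit leaves some children contributing one condition.

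At stake is whether a small or null primary result could be taken at face value.

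**Working it through.** **1. The plan's own figure.** Inputs from *Power calculations and statistical analyses*: SD 870 kJ, within-person correlation 0.7, difference 250 kJ, 80% power, p < 0.05 (taken as two-sided).

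- SD of the paired difference = 870 × √(2 × (1 − 0.7)) = 673.9 kJ.
- Normal approximation: n = (673.9 × (1.960 + 0.842) / 250)² = 57.0, so 58.
- The exact paired t test gives 80.0% power at n = 59. The stated 59 reproduces.

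**2. Power after the exclusion.**

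- 110 × 0.80 = 88 evaluable children; power for 250 kJ is 93.1%.
- Applying the pilot rate on top: 88 × (1 − 2/11) = 72; power is 87.4%.
- Both exceed the stated 80%. The pilot rate is very imprecise: 2/11 = 18%, exact 95% interval about 2% to 52%.

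**3. Possible bias.** None of these inputs is in the document; they are assumptions to show scale:

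- 6% of extension visits are not full.
- Restriction shifts a latent normal fullness score down by 0.5 or 0.8 SD.
- Within a visit, fullness correlates −0.3 to −0.5 with free-access intake.
- Between a child's two visits, fullness correlates 0 or 0.5.
- Only children full at both visits are analysed.

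With fullness independent between visits there is a closed form. Write λ(x) = φ(x) / (1 − Φ(x)), with cut-point c = Φ⁻¹(0.06) = −1.555. The within-child SD of intake is 870 × √0.3 = 476.5 kJ, and

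bias = 476.5 × r × [λ(c + shift) − λ(c)].

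- λ(−1.555) = 0.127, λ(−1.055) = 0.268, λ(−0.755) = 0.387.
- Shift 0.5 SD (14.6% of restriction visits not full): 476.5 × 0.141 = 67.2. For r = −0.3 the bias is −20 kJ, so 250 becomes 230; for r = −0.5 it is −34 kJ, giving 216.
- Shift 0.8 SD (22.5% not full): 476.5 × 0.2605 = 124.1. The biases are −37 and −62 kJ, giving 213 and 188 (187 in simulation).

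With a between-visit correlation of 0.5, simulation gives about 234 to 225 kJ (0.5 SD) and 221 to 203 kJ (0.8 SD), within a kJ or two. With no shift, or with zero within-visit correlation, the mean stays at 250 kJ.

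Across these settings 250 kJ averages about 187 to 234 kJ, a loss of 16 to 63 kJ. The standard error at n = 72 is 673.9 / √72 = 79.4 kJ, so the bias is about 0.2 to 0.8 of a standard error.

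**4. Visit or child.** A second set of assumptions has 5% of extension and 15% of restriction visits not full, fullness correlated 0.5 between visits and −0.3 with intake between children, and a within-visit correlation of 0 to −0.5. A true 250 kJ then becomes 221 to 249 kJ among children full at both visits, and 198 to 225 kJ as a simple difference of means over full visits. The second is not the planned mixed model, but it shows that the unstated choice can matter. With 10% not full in both conditions, both versions return 250 kJ.

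**The case against.** The strongest reply is that the rule is part of what is being measured. The aim is intake in the absence of hunger, and snacking by a child who is still hungry is something else. If restriction lowers fullness, an all-children analysis counts more hunger-driven eating under restriction and could overstate the effect on that construct. This stands. A reader might infer that the all-children set must replace the restricted one as primary. The document does not support that: the two analyses answer different questions, and the case is for reporting both.

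The procedure also works to equalise fullness. The buffet offers 14,883 kJ, staff encourage further eating, and pre-load intake is itself measured, so a child who is harder to satiate can eat more before rating 4 or 5. This should reduce exclusions, but the pilot still had two.

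The hypothesis concerns appetite regulation and eating for reasons other than hunger. It does not predict a lower score on the scale after an encouraged meal. A reader might infer that the strongest responders to restriction are the ones removed, but nothing in the document shows this.

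Two further inferences also fail. The trial is not left underpowered, and the 20% allowance for drop-out and incomplete data may already cover these exclusions, so taking off a further 18% may count them twice. Nor is it fixed that one non-full visit discards the child's pair; the mixed model could keep the other visit.

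Finally, an unseen analysis plan may add sensitivity analyses. The exclusion itself, however, is fixed in this article.

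**Conclusion.** The point holds as a conditional risk to the primary contrast and should be fixed. The plan selects on a response measured after treatment, in a domain that treatment is expected to affect, and nothing in the article would reveal the consequences. Whether bias occurs depends on fullness rates differing by condition, which is plausible but not shown. Its direction and size depend on correlations that the document does not give. If rates differ as assumed above, the result is a moderate attenuation, to about 187 to 234 kJ from 250 kJ; if they do not, little or no bias is expected. The document does not support saying that the primary result will be biased.

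**What to change.** Amend the feeding-experiment section and *Power calculations and statistical analyses* to:

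- prespecify an analysis of all randomised children with free-access intake, at every visit and whatever the fullness rating, reported beside the fullness 4 or 5 analysis;
- report the number of non-full visits by sleep condition;
- state whether a non-full rating drops the visit or the child;
- claim an effect on eating in the absence of hunger only if the two analyses agree, with agreement defined in advance.

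The cost is wording. The article does not say that non-full children skip the free-access phase, so their intake should already be collected. The small downside is that the all-children estimate includes some visits where the child was not fully satiated and is slightly less specific to the absence of hunger. Keeping the restricted analysis beside it limits that loss.

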#### Diet recalls (secondary aims 1, 2 and 3)

Children (assisted by their caregivers) will be interviewed about the child’s dietary intake on the third day and the last day of each experimental week (weeks 3 and 5) using multiple pass 24-h recalls, the type of method used in the NZ Children’s National Nutrition Survey **[**65**]****.** In-person diet recalls will occur on the days directly after the cameras are worn (see below). Caregiver/child dyads will be interviewed in person about their child’s dietary intake (from midnight to midnight), on 2 days during each test week (ensuring all days of the week are represented across conditions). Collecting two 24-h recalls will the calculation of ‘usual intake’ using the Multiple Source Method for estimating usual dietary intake **[**78**]****.** This method takes into account day-to-day variation so that each participant’s intake estimate for that week will be more representative of the whole week, rather than being overly influenced by one extreme day. The first step will collect a quick list of all foods and beverages consumed the previous day in the 24-h midnight to midnight period. Next, information will be sought regarding the time and place of eating, which act as memory cues to help the participant remember the details about food in the next step. In step three, comprehensive details regarding each food or beverage item will be collected including brand name, cooking method, and portion size. A variety of aids will be used to assist with portion size estimation including photographs of commonly consumed foods, and using dried beans to estimate the volume of food consumed (this can be converted to grams of each item using known data on density where weight = volume x density). A list of typical forgotten foods will be presented (e.g. beverages, sweets, snacks), which can account for up to 6% of energy each day **[**79**]****.** Finally, the recall will be reviewed and additional foods probed **[**79**,**
80**]****.** The diet recalls will be recorded on paper and subsequently entered into FoodWorks 9 Professional® using the Otago Food list 2018 **[**81**]****,** and energy intake will be calculated and compared between extension and restriction interventions. Change in food group consumption will also be compared.

#### Wearable cameras (secondary aims 1, 2, 3)

Participants will wear a small camera (Brinno TLC130), set to automatically take a photograph every 2 seconds for 2 days during each test week; the cameras will be worn during all waking hours on the days prior to collecting the in-person 24-h diet recall interviews. Thus the camera images assess the same day as the recalls, as 24-h diet recalls assess the previous day’s intake. By timing the outcome measures in this way, the images can be reviewed in order to seek any clarifications to improve the accuracy of dietary recalls conducted by field researchers to elucidate food intake that appears in the camera images but not the diet recalls. Studies in adults have shown that the addition of these images reduces under-reporting of foods [82, 83], particularly snacks [37], although little work has been undertaken in children. The images will also be used to map the context behind eating on these days, providing insight into alterations in food choice in the free-living environment [83, 84]. Once images containing foods have been identified these images will be coded using the open source software TimeLapse2, which allows users to configure their own coding schemas and generate a database as images are coded. Images will be coded to determine information on food type (342 possible codes), location of consumption, length of eating occasion, presence of other people, and simultaneous participation in other activities [40]. Participants and their caregivers will have the option to view these photos prior to the researchers seeing them, and will have the opportunity to delete what they want, to maintain privacy. We have previously used this method to code screen images in teenagers [85]. Any images used for presentation purposes will require written consent from families, and any third party individuals faces will be blurred.

We will follow the ethical framework developed by Kelly et al [86] which guides researchers using automated wearable cameras and considers participant privacy, anonymity and storage of data. Participants and their families will be offered the opportunity to view and delete images before the research team views them. During the study participants will also be able to remove the camera or turn it off and on when they require privacy. Images will be stored on a secure server only accessible to researchers involved in the study. All data will be anonymised using participant ID. The camera may capture third-party members of the public including minors. Any identifying features within an image will be blurred before any image is used for publication or presentation purposes. Participants will carry an information card which they can give to members of the public explaining the study. They will also be instructed to simply remove the camera if asked to do so.

#### Questionnaires (end of each experimental week)

##### Changes in eating behaviour (secondary aim 3)

Primary caregivers will complete the 35-item Child Eating Behaviour Questionnaire (CEBQ) [64], which provides eight subscales including satiety responsiveness (how well they eat to appetite), food responsiveness (eating for reasons other than hunger), emotional over-eating (eating because of emotions), and fussiness. Questions will be adapted to reflect the past week.

##### Assessment of mood and sleep impairment/disturbance (secondary aim 3)

Children will complete the 27-item Kidscreen questionnaire which assesses mood and quality of life over the past week [61], and the 16-item PROMIS patient-reported outcomes measurement information system (PROMIS) questionnaire which assesses sleep disturbances [62] (difficulties falling and staying asleep) and sleep impairment [62] (impact on daytime functioning) over the past week. Caregivers will complete a proxy version of the PROMIS questionnaire (providing different perspective of the outcomes).

##### Food cravings questionnaire (secondary aim 4)

The food cravings questionnaire is a computerized task that measures the desire to eat a variety of foods based on an American model [32, 33] modified to represent New Zealand foods. Children will be shown pictures of a variety of foods (n = 60) differing in nutritional quality, including core and non-core foods. ‘Core’ foods form the five food groups (fruit, vegetables, cereals, meat and alternatives, and milk and alternatives), and ‘non-core’ foods are everything else, defined by fat and sugar cut-off points derived from dietary guidelines [87]. Participants will be asked to rate the appeal of each food on a sliding scale reflecting how much they want to eat that food right now (from “*Heaps!*” to “*Not at all*”). It is anticipated that the treat foods will be rated more highly after sleep restriction.

